#### Data analyses

All analyses will be undertaken in Statistical Package for the Social Sciences (SPSS) version 25 (IBM SPSS, IBM Corp., Armonk, NY, USA) using re-identifiable (i.e., coded) data. Data analysts will not be blinded to study arm. Descriptive statistics will be used to summarize participant demographic and obstetric data. Group differences in baseline variables will be examined using cross-tabulations, independent *t*-tests, and regression analyses, with differences in baseline outcome measures controlled for in further analyses. To determine program efficacy, intention-to-treat linear mixed models will be estimated for each outcome measure, with restricted maximum likelihood (REML) estimation used to account for missing data due to participant dropouts [60]. These models will yield more accurate estimates of effect compared to completer as they account for the unbalanced nature of the data [60, 61]. Mixed models will be estimated separately for each outcome variable, with time, group, and time by group interaction entered as fixed factors. Comparisons within and between groups from baseline to 3-month follow-up for each group will be undertaken for outcomes. Between-group effect sizes will be calculated using the pooled standard deviation of the estimated marginal means and adjusted for sample size (Hedges *g*). Effect sizes of 0.20, 0.50, and 0.80 are considered small, moderate, and large respectively [62]. Descriptive statistics will be used to summarize participant engagement, adherence, and program satisfaction data.

A cost-utility analysis comparing the program’s efficacy and acceptability against usual care in a primary care setting will be conducted. Analyses will be based on direct and indirect costs associated with program development, evaluation, and participants’ social opportunity costs (e.g., work productivity, absenteeism, and presenteeism). The health economic evaluation protocol and findings from this trial will be published separately.

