#### Randomization and allocation procedures

Following completion of baseline questionnaires (timepoint 1), participants are randomized online between the intervention (LWL group) and care as usual control condition (CAU group). Randomization is based on a 1:1 ratio using random permuted block randomization, with block sizes of 2, 4, and 6 to ensure equal numbers of participants in each study arm. Randomization is stratified by two variables: relationship to baby (mother who carried baby vs partner) and distress severity at baseline (low distress vs moderate-to-high distress) to ensure equal distribution across both study arms. The allocation sequence was generated by a biostatistician and uploaded to the LWL course delivery system by an IT consultant, both independent to the conduct of this trial. The course delivery system is coded to randomize participants, based on the allocation sequence, immediately following completion of baseline questionnaires. The allocation sequence is concealed from the research team for the duration of the study. Once participants have been randomly allocated to a study arm, they will be automatically logged into their online participant portal and notified of group allocation on their home page. Once allocated to a study arm, both participants and research personnel will not be blinded to group allocation.

Participants in both study arms will be able to access usual care and support services during the 21-week trial period. Such care is expected to include a heterogenous mix of professional and non-professional supports and interventions, and will be assessed at each primary timepoint. Contact between participants and research personnel will be: (1) in response to participant request for technical support; (2) initiated by the trial clinician for the purpose of safety monitoring; or (3) initiated by the research team if a participant has been inactive for more than 14 days following assessment timepoints. No further outcome data will be collected for participants that withdraw or drop out. Participants are encouraged to tell their general practitioner (GP; Family Doctor) that they are participating in this research trial as part of the intervention or control study arm.

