#### Primary outcome—psychological distress

The Kessler Psychological Distress 10-item scale (K10) [40]—a self-report scale to assess symptoms over the past 4 weeks. Items are rated on a 5-point scale from 1 (none of the time) to 5 (all of the time). In addition to the three primary timepoints, participants in the LWL group will also complete the K10 once per week while completing the intervention to monitor for potential harmful effects of the intervention such as symptom deterioration [45]. The K10 has strong psychometric properties, is sensitive to change (i.e., in tracking symptom changes in response to treatment [46]), and has been used in efficacy studies of digital mental health interventions including perinatal populations [21, 22] and in the context of grief [47, 48].

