### Data management and monitoring

This study is co-ordinated and managed by the Stillbirth CRE located at Mater Research Institute (MRI) within The University of Queensland Faculty of Medicine in Brisbane, Australia. All participation procedures and data collection will be conducted through the custom-built LWL online course delivery system managed by the coordinating research team based at the Stillbirth CRE. Re-identifiable data only (i.e., coded) will be exported weekly from the LWL course delivery system by a member of the research team and stored in accordance with Stillbirth CRE data management specifications. There is no data monitoring committee or planned interim analyses given this is a short-term small study involving a low-risk intervention. Participant safety is monitored by the trial clinician as part of the intervention. A steering group has been established to oversee and review data validity and overall conduct of the trial. This steering group includes clinicians, researchers, parent support and advocacy organizations, and bereaved parents who collectively provide specialist knowledge of design and conduct of RCTs, perinatal bereavement care and mental health, and lived experience of perinatal loss.

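### Analysts who know the arms decide, with no stated threshold, which baseline differences to adjust for; fix the covariates in advance and mask the arm codes

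*Protocol article*

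**What the plan says.** The protocol article's Data analyses section states "Data analysts will not be blinded to study arm" and gives no reason. Its rule for adjustment begins "Group differences in baseline variables will be examined using cross-tabulations", adds t-tests and regression, and ends "with differences in baseline outcome measures controlled for in further analyses". The section gives no threshold for a difference and no list of covariates. The core of the model is fixed: a REML mixed model for each outcome, "with time, group, and time by group interaction entered as fixed factors".

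Three other sections bear on the point.
- **Randomization and allocation procedures:** "Once allocated to a study arm, both participants and research personnel will not be blinded to group allocation". The same section says "Randomization is stratified by two variables", namely relationship to baby and distress severity at baseline. Data analyses does not name either as a covariate.
- **Data management and monitoring:** "Re-identifiable data only (i.e., coded) will be exported weekly from the LWL course delivery system by a member of the research team".
- **Primary outcome:** the K10 is self-reported, and "participants in the LWL group will also complete the K10 once per week while completing the intervention". These weekly scores exist in one arm only.

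**The concern.** Participants and staff know the allocation and the primary outcome is self-reported, so the analysis is the one stage left where the arms could be masked. The plan declines to mask there. It also leaves a modelling choice open at that same stage: someone must judge whether baseline PGS, GAD-7 or EPDS scores differ enough to be controlled for, and that person will know which arm is LWL.

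In a randomized trial, baseline differences between arms arise by chance. A baseline test therefore says nothing about whether a covariate is prognostic, which is the proper ground for adjusting. At stake is the credibility of the efficacy estimates: a reader cannot rule out that the covariate set was settled with the treatment effect in view.

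**Working it through.** The plan gives no figure on this point, so there is none to reproduce. The check was a simulation under no treatment effect.

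**Inputs from the protocol article.** N = 150 at 1:1 gives 75 per arm. With 25% dropout, 75 × 0.75 = 56.25, taken as 56 per arm. Within-subject correlation is 0.5 and alpha 0.05 (taken as two-sided).

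**Assumptions.** Six baseline outcome measures (K10, PGS, GAD-7, EPDS, DRS, AQoL-8D), equally correlated with each other and with the 3-month outcome, at 0.5 or 0.7. A linear model of the 3-month value stands in for the mixed model. Stratification is ignored. There were 5,000 runs per setting, so the Monte Carlo standard error at 5% is √(0.05 × 0.95 / 5000) = 0.0031, or 0.3 percentage points.

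**Results: two-sided type I error, nominal 5%**

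| Covariate policy | correlation 0.5 | correlation 0.7 |
|---|---|---|
| Baseline K10, fixed in advance | 5.2% | 5.0% |
| Adjust for any measure with baseline p<0.05 | 3.2% | 2.6% |
| Smallest p among eight covariate sets | 12.1% | 14.1% |

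The eight sets are: none; K10 alone; K10 plus one of the other five; all six (1 + 1 + 5 + 1 = 8).

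**Mechanical rule.** It falls below 5% by far more than simulation error. When chance imbalance at baseline would carry through to the outcome, the rule tends to adjust it away; when the rule is not triggered, the unadjusted test is slightly too cautious. At least one measure was triggered in 21% (0.5) or 16% (0.7) of trials. Independent measures would give 1 − 0.95⁶ = 26.5%; correlation lowers this.

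**Does masking stop selection?** The test statistic is t = b/se(b). Swapping the labels turns b into −b and leaves se(b) unchanged, so |t| and the two-sided p-value are the same. An analyst with codes A and B who picks the smallest p therefore also reaches 12.1% or 14.1%. By symmetry about half of these errors favour LWL: 12.1/2 = 6.1% and 14.1/2 = 7.1%. An unmasked analyst picking the most favourable model for LWL reaches 5.9% or 7.2%, against a nominal 2.5%. The two are essentially equal. Masking hides which direction favours LWL; only a covariate set fixed in advance brings the error back to 5%.

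**Can the arms be masked?** The efficacy models need only measures taken in both arms at baseline, post-intervention and 3 months. The data that reveal the arm (weekly K10, module and program satisfaction, usage) are LWL-only and play no part in those models. Data are already coded at export, so an A/B file is feasible, but the team member who exports now is not blinded.

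**The case against.** The strongest reply is that the rule is narrower than it looks. It concerns baseline outcome measures only, depends on baseline rather than on results, and sits inside a named model with fixed terms. Applied mechanically it is conservative. Stratifying by distress severity limits imbalance in K10. The trial is prospectively registered with a named primary outcome and timepoint. A threshold and covariate list are commonly left to a statistical analysis plan, which is not shown.

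Most of this stands. The missing threshold alone would be no finding. What the article does fix is a data-driven trigger and analysts who know the arms, and neither is a detail awaiting a later document.

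Three stronger readings are tempting and not supported.
- A reader might infer that the plan as written inflates the type I error. The simulation shows the opposite for mechanical use, and the 12% to 14% rates need deliberate selection among covariate sets, which the text does not license.
- A reader might infer that masking would cure the problem. It cannot, because two-sided p-values ignore labels.
- A reader might infer that masked analysts would protect the outcome measurement. The K10 is reported by participants who know their arm, and nothing done at analysis changes that.

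**Conclusion.** The point holds in limited form. The plan gives an undefined judgement about baseline differences to analysts who know the allocation. Followed mechanically at p<0.05 the rule costs some efficiency and rejects in about 3% of null trials, so no inflation can be charged to it. The exposure is to discretionary use. The 12.1% to 14.1% rates show what free choice among eight covariate sets could do; they do not predict conduct. They depend on the assumed correlations, on six measures, on the stand-in model and on the menu of sets.

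Setting the covariates in advance is the effective remedy. Masking is a useful addition, because it takes away knowledge of which direction favours LWL. Neither change affects the sample size. The matter is worth correcting but does not invalidate the design.

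**What to change.** 1. **Covariates.** Replace the baseline-test trigger in Data analyses with text such as: *Each efficacy model will adjust for the baseline value of its outcome, relationship to baby and baseline distress severity. Baseline significance tests will not be used to select covariates.* Also say whether baseline enters as a covariate or as the first repeated measurement, so that it is not used as both.

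2. **Masking.** Replace the sentence on unblinded analysts with: *A person outside the analysis will export the three-timepoint outcome file with arms coded A and B. LWL-only data (weekly K10, module, satisfaction and usage data) will be held in a separate file. The primary and secondary efficacy models will be run and locked before the codes are revealed.*

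3. **Date the change.** Recruitment began on 28 June 2021 and follow-up lasts 21 weeks. By the 1 February 2022 status report about 31 weeks had passed (218 days / 7), so some 3-month data may already have been exported. The amendment should record what the team had seen. The proposed covariates follow from the design and need no look at the data.

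The cost is an amendment, one extra export step and someone outside the analysis to do it. Masking may be imperfect if dropout differs visibly between arms.

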### Participants and recruitment

An opportunity sample of self-selecting participants will be recruited via a snowball sampling strategy. Parents and healthcare professionals will be notified of this trial through online and social media advertising, flyers at local maternity services (e.g., Mater Mothers’ Hospital, Brisbane, Australia), and by word of mouth (e.g., healthcare professionals; parent support organizations). All parents interested in participating are directed to the LWL website to review participant information and express interest. This trial aims to recruit at least 75 participants in each study arm (total *N* = 150) which allows for an anticipated dropout rate of 25% (see Statistical methods). Participants will be recruited over a 12-month period.

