### Statistical methods

#### Sample size calculation

As the primary outcome in this trial is both continuous and measured longitudinally, we employed the sample size calculation suggested by Diggle and colleagues [59]. Assuming a significance level of 0.05, 80% power, a moderately strong within-subject correlation (*ρ* = 0.5), three timepoints, and an anticipated dropout rate of 25%, a minimal total sample size of 150 participants is required to detect a standardized difference (Cohen’s *d*) of 0.5 (i.e., a “moderate” difference between groups). This power calculation was informed by published RCTs of brief digital mental health interventions for posttraumatic stress and prolonged grief in parents after the loss of a child during pregnancy [29] and psychological distress, anxiety, and depression in postpartum women [22].

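### Baseline adjustment is made to depend on observed differences between arms; fixing it in advance would add about 8 points of power at the protocol's own correlation

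*Protocol article*

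**What the plan says.** The protocol article, under Data analyses, first plans a comparison of the arms at baseline: "Group differences in baseline variables will be examined using cross-tabulations, independent *t*-tests, and regression analyses". The sentence ends "with differences in baseline outcome measures controlled for in further analyses". It sets no significance level or size of difference that would trigger control, and does not say how the control would be done. The same paragraph states "Data analysts will not be blinded to study arm".

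The efficacy model is a REML linear mixed model, fitted separately for each outcome. Its fixed effects are time, arm and their interaction. Neither a baseline covariate nor a stratification factor is named. The Abstract defines the primary outcome as change in K10 from baseline to 3 months, and Table 2 lists K10 at all three main timepoints, so baseline K10 enters as a response.

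Under Randomization and allocation procedures, allocation is stratified by relationship to the baby and by baseline distress severity (low against moderate-to-high). The scale and cut-point for the second factor are not named there.

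**The concern.** Under randomisation any baseline difference arises by chance, so examining it does not answer the useful question. Adjustment helps when the baseline score predicts the follow-up score, whether or not the arms happen to differ. The protocol already assumes such prediction, with a within-subject correlation of 0.5.

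Two things are at stake. The first is precision on the primary outcome: if no difference is declared, the model keeps a free baseline mean in each arm and gives up information that randomisation provides. The second is pre-specification: the covariates are settled after the data are seen, by people who know the allocation, on a criterion that is not written down.

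**Working it through.** **Inputs.** From Sample size calculation: significance level 0.05, 80% power, correlation 0.5, three timepoints, 25% dropout, d = 0.5, total 150. From Participants and recruitment: 75 per arm. Assumed: two-sided testing, equal correlation between all pairs of timepoints, outcome SD of 1 at each time.

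**The plan's own figure.** The protocol says "a minimal total sample size of 150 participants is required to detect a standardized difference" of 0.5. No single standard variant returns 150. A two-sided comparison of change scores (or of follow-up scores alone) needs 126 completers, which is 168 after dividing by 0.75. Baseline-adjusted analysis needs 96, which becomes 128. The three-timepoint average needs 84, which becomes 112. This is a separate matter; the power figures below start from 150 as given.

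**Step 1, closed form with completers only** (0.75 × 75 ≈ 56 per arm):
- Change score: SE = √[2 × 2(1 − ρ)/n] = √(2/56) = 0.189; power = Φ(0.5/0.189 − 1.96) = 75.4%.
- Baseline-adjusted: SE = √[2(1 − ρ²)/n] = √(1.5/56) = 0.164; power = 86.3%.

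The gap is 10.9 points, but this is not the planned analysis, because the mixed model also uses the earlier data of those who drop out.

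**Step 2, the planned mixed model.** The information matrix is the sum over dropout patterns of n·X′V⁻¹X, with 75 per arm and 25% missing at 3 months, half of them already missing at week 8. The treatment effect is the arm difference in change from baseline to 3 months, with baseline means free or constrained to be equal.

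| Correlation | SE, free baseline | SE, common baseline | Power, free | Power, common | Gain (points) |
|---|---|---|---|---|---|
| 0.3 | 0.213 | 0.179 | 65% | 80% | 14 |
| 0.5 | 0.181 | 0.162 | 79% | 87% | 8 |
| 0.6 | 0.163 | 0.149 | 87% | 92% | 5 |
| 0.7 | 0.142 | 0.133 | 94% | 96% | 2 |

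At 0.5 the standard error falls by 11% (1 − 0.1620/0.1814). Putting all dropout before week 8, or all after it, moves the free-baseline power only between 78.2% and 79.1% and the common-baseline power between 86.5% and 87.4%; the gain stays at 8.3 points. The total needed for 80% power is 150 × (SE × 2.80/0.5)², which is 156 with free and 124 with common baseline means, rounded up to equal arms.

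**Step 3, how often the rule would act.** This needs assumptions the document does not supply: a trigger of p < 0.05, K10 as the stratifying scale, and a cut-point. In 5,000 simulated trials per setting, with stratified blocks and cuts at the 20th, 35th, 50th and 70th percentile, the baseline K10 t-test was significant in 0.1% to 0.6% of trials. Without stratification it was about 5%, which is also the chance rate for each outcome not used in stratification. Under these assumptions the test-then-adjust rule had the same power as never adjusting.

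**Step 4, validity.** In a simulation with no treatment effect and a median cut, the unadjusted change-score analysis that left the stratum out had a type I error of 3.9%, which is conservative.

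**The case against.** The strongest defence is that baseline K10 is already in the model. The contrast of interest is change from baseline, so chance imbalance is removed without a covariate. This stands. A reader might infer from the rule that the primary result would be biased or its error rate inflated, but nothing in the document or the calculations supports that. What is lost is efficiency.

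A reader might also take the loss as 10 points or more. That is the completer-only figure of Step 1. The planned REML model gives about 8, and the planned analysis falls only 1 to 2 points short of the stated 80%, so the trial is not seriously underpowered by this choice.

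It is tempting to say that the rule would almost never act for K10. The document states no test threshold, no scale for the distress stratum and no cut-point, so this holds only under the assumptions of Step 3. If any visible difference were enough, adjustment would be more frequent. The two harms also trade off: the less often the rule acts, the more settled the K10 model is; the more often it acts, the smaller the power loss. Dependence on the data therefore matters more for the outcomes not used in stratification.

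Lastly, one might infer that baseline K10 would be used twice, as response and covariate. The document does not say how differences would be controlled for, so this cannot be asserted.

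The defence does not remove the main point. The document fixes a method in which adjustment waits on observed differences, and that is not a detail left to a later plan.

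**Conclusion.** The point holds as one of efficiency and pre-specification. Control for baseline outcome measures depends on observed differences, with no stated criterion and with unblinded analysts, while the default model is valid but less precise than it need be. At the protocol's inputs, committing to baseline adjustment raises power from 78% to 79% up to about 87%. The size rests on the assumed correlation of 0.5, compound symmetry and two-sided testing, and shrinks to about 2 points at a correlation of 0.7. If the trigger is a 0.05 test and the distress stratum is cut from K10, this precision would usually be forgone for the primary outcome, and each outcome not used in stratification would trigger adjustment by chance about 5% of the time. This should be fixed before analysis, but it does not invalidate the planned comparison.

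**What to change.** Delete the rule that ties adjustment to observed baseline differences. State in advance that every efficacy model adjusts for the baseline value of its own outcome, whatever the imbalance. The preferred form keeps baseline as a response and gives both arms one common baseline mean, with arm effects only at post-intervention and 3 months. This keeps participants without follow-up data in the intention-to-treat model; a model with only the follow-ups as responses would drop them.

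Include the two stratification factors, relationship to the baby and baseline distress severity, in every model. If the distress stratum is cut from K10, let its effect differ by timepoint in the K10 model, since such a stratum separates baseline scores more than follow-up scores.

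The cost is one paragraph of analysis wording. All the scores needed are already collected at baseline and no participants are added. Under Trial status, 62 participants had been allocated and recruitment was continuing at 1 February 2022, so at that date the change could precede analysis. Because the analysts are unblinded, it should be dated and recorded before outcomes are compared by arm.
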